**1. PROJECT TITLE**

Effect of Packaging on Smoking Perceptions and Behavior: A Randomized Trial

**4. ESTIMATED DURATION OF THE STUDY**

5 years

**6. SPECIFIC AIMS**

**Primary Aim 1:** To test whether removing all tobacco industry imagery from the standard US pack (plain packs using current US warning label, white on black) changes consumer perceptions of their cigarettes. We hypothesize that a gap will develop across study groups (AM > PP > ST) with:

- a) increased perceptions of risk from tobacco use, decreased perceptions of appeal of packs and decreased subjective reinforcing effects from their tobacco use
- b) greater between-group differences during the intervention period than during 12-month follow-up.

**Primary Aim 2:** To test whether adding large graphic warning labels to the plain packs of Aim 1 (the Australian model pack) increases the perception of harm and potential risk of tobacco products. We hypothesize that over the three months of the intervention, smokers assigned to AM compared to PP or ST will report:

- a) increased change in reported awareness and concern about the health hazards of smoking

- b) decreased willingness to display the pack in public

**Primary Aim 3:** To test whether the Australian model packs result in a change in the handling of cigarette packs, consumption patterns and quitting cognitions. We hypothesize that, compared to objective assessment of behavior when handling ST packs, we will observe greater behavioral change with AM packs than PP, in:

- a) greater attentional demand to warning label, changes in handling the pack, obscuring of warning labeling during a cigarette offer challenge, greater recall of warning label messaging
- b) greater reductions in tobacco use during the 3-month intervention, validated by saliva cotinine.
- c) increased reports of motivation and intention to quit during the 12-month follow-up

## 7. BACKGROUND AND SIGNIFICANCE

The first country to require health warning labels on tobacco packs was the US in 1966. However, there has been little meaningful change in these text-only messages since then and the imagery and branding on many cigarette packs make messages difficult to read. The salience and recall of warning labels improves when the messages are distinguishable from the package design. Larger text-based warnings are associated with increased risk perceptions and improved health knowledge. Following early reports on their effectiveness of graphic warning labels, in 2003, the WHO Framework Convention on Tobacco Control required the use of large, rotating health warnings on all tobacco products, packaging and labeling, recommending that full color pictures or pictograms be mandated. As of the end of 2011, over 39 countries, but not the US, had implemented pictorial health warnings on cigarette packages (FDA, 2012).

Tobacco companies have used cigarette packaging design to downplay the risks of smoking through the use of brand descriptors, pack colors, brand variant names, and numeric tar and nicotine labels (Wakefield et al, 2002). As a result, both adult smokers and youth believe that low tar or light cigarettes are less harmful and less addictive than regular strength brands, and many smokers switch to lower tar brands instead of quitting.

The marketing effectiveness of pack design prompted proposals to introduce plain cigarette packaging. These “standardized” packaging regulations would (1) strip packs of colors, brand imagery, corporate logos, and trademarks; (2) have the brand name in a mandated size, font and location; and (3) feature health warnings and other legally mandated information. Evidence from multiple sources suggests that both plain packs and graphic health warning labels are associated with changes in risk perceptions among smokers and may be associated with increased quitting and a reduction in daily consumption. However, this evidence relies heavily on hypothetical experiments and from population surveys before and after implementation of national policy changes that included changes in package design. Studies where participants have switched to using new cigarette pack designs have been compromised by short exposures, significant participant burden and high attrition. Although there may be significant public health impact from changing pack designs, controlled evaluations of the persistent impact of proposed changes to labeling are unavailable (Hammond et al, 2011). The United States is now one of the few high-income countries that can conduct such trials. In recent decades, the US has been a laggard in using the cigarette pack to inform on the health hazards of smoking. It would appear that the quality of evidence demanded by the Appeals court judge in order to limit the commercial speech of the tobacco industry on cigarette packages in the US, will require rigorous randomized controlled trials among US populations of smokers.

## 8. PROGRESS REPORT

Not Applicable.

## 9. RESEARCH DESIGN AND METHODS

### 9.A. Overview

Much of the current research base on pack design and consumer perceptions has relied upon single-occasion experimental assessment, using hypothetical scenarios to measure expectations, and has relied on images of packs rather than actual packs in cued-reaction tasks. It is now possible to have objective behavioral assessment of real-time consumer interactions with professionally produced cigarette packaging. These objective behaviors can then be connected with mobile technology to allow intensive capture of day-to-day changes in perceptions and tobacco use behavior in the context of the consumers' typical environment. We have licensed from the Australian Government Department of Health, the strongest images of tobacco-related harms currently in use. This unprecedented randomized controlled trial will provide a unique opportunity to examine smokers' acute and persistent adaptations to proposed policy recommendations to change the labels and marketing materials on US cigarette packaging.

The real world experience in Australia demonstrates that smokers can continue to smoke with large graphic warning labels (Wakefield et al., 2008). We will conduct our randomized study by producing packs to specifications used in the real world setting of Australia, and filling them with the cigarette brand of the smoker. This will significantly reduce participant burden and should allow us, with appropriate incentives, to achieve 6 times the exposure to these packs as in the best of previous studies. We will use a conjoint marketing study to predict participant response, including unwillingness to continue with the study exposure. Further, we will use interactive text messaging to measure cognitions in real time rather than rely on recall, thus removing another major bias of currently available studies. Finally, we will use the new Kinect 3-D and Leap motion-sensor technology to capture real-time objective behavioral data of participants display cigarette packs when offering a cigarette to a research associate. All questionnaires will be web-based to minimize participant burden further. Thus, our study should significantly add to the knowledge base for tobacco regulatory science.

### 9.B. Approach

**9.B.1. Study Overview: Figure 1** shows community recruitment of the study sample of smokers of popular brands of US cigarettes (the top 75% of market share). There will be three major periods within this study.

**9.B.1.a Run-In-Period** At the initial contact eligible participants will complete all baseline lab and self-report assessments. There will then be a 1-month run-in period during which they will purchase their US branded cigarettes from the study at the study discount price. In order to proceed to randomization and the rest of the study, eligible smokers will need to complete at least 2 purchases from the study as well as the study assessments required for this period.

**9.B.1.b. Purchasing Intervention Period** After participants have been randomized to purchase their preferred brand of cigarettes from one of 3 cigarette-packaging groups (AM, PP or ST packs), the purchasing intervention will last 3 months, during which smokers will interact with daily text-message and use assigned

[figure not shown]

packs. We will monitor compliance via text messages, provide multiple points of access to the study vendor and use a price incentive to maximize adherence to purchasing cigarettes from the study.

**9.B.1.c. Post-Intervention Follow-up Period**, After 3 months, participants will go back to purchasing cigarettes from their usual sources and follow-up will continue through 12 months.

**9.B.1.d. Assessment overview**: Clinic visits will occur at three time points: at the beginning of the run-in period, at the end of both the purchasing and the post intervention periods. Each clinic visit will be preceded by the completion of a web-based questionnaire, will include collection of a saliva sample and the participant will go through routinized cigarette handling tasks that will be recorded using objective multi-modal sensor-based behavioral monitoring. Lab-based behavioral assessment will allow detailed objective metrics of handling of usual brands, initial behavioral reactions to AM and PP packs, cognitive processing and behavioral interaction with warning labels, and objective assessment of whether smokers change or accommodate handling of packs after 3-months of using ST, AM, or PP. During the run-in period, all participants also will complete a web-based conjoint trade-off study to assess how each element of the AM and PP designs change perceptions of marketing materials, design features, personal relevance of warning messages and value of each product. Throughout each of the study periods, participants will receive a series of interactive text messages as part of our ecological momentary protocol to assess *perceptions* (appeal of packs, subjective effects on product consumption over time), pack use behavior (avoidance, willingness to display), and *effectiveness of warning label communication* (awareness of harms over time, quitting cognitions). Using the self-report assessments at baseline, 5- and 12-month visits, we will assess the following primary domains: a) participant characteristics, including potential moderators; b) marketing materials: salience, receptivity, and perceived attributes; c) tobacco use effects and cognitions; d) environmental influences. This study will provide objective behavioral data, detailed assessment of the impact of packs in the context of smokers' typical environment, and allow these acute and long-term effects to be evaluated in a randomized controlled trial.

**9.B.2. Recruitment**: We will recruit 450 current smokers who use on of the five most common brands as their usual brand and who live in the San Diego area. Standard media announcements will be used to recruit for this study including print, online bulletin boards, social media, website and community outreach strategies will be used to recruit. We also have ongoing recruitment opportunities with email and print notifications within UCSD Family Medicine clinics serving approximately 30,000 patients through more than 150,000 office visits. [name] will liaison with community networks of providers throughout the region to extend recruitment efforts to community health agencies.

**9.B.3. The Initial Clinic Visit**: Participants will attend a baseline assessment meeting at the UCSD CTRL. During this clinic visit, staff will provide them with study details and allow them to handle the packs for the different study groups. Participants will provide a saliva sample for later cotinine analysis and complete a short survey of their usual cigarette purchasing behavior (including frequency of purchase), their current smoking pattern, the last time they smoked a cigarette other than their usual brand, quitting history and readiness to quit as well as the questions from the Australian multiple cross-sectional survey. They will be introduced to the study vendor website for purchase of discounted cigarettes and commit to using this website as their only vendor for cigarettes for the next 4 months (1-month run-in and 3-month intervention).

**9.B.4. Behavioral Assessment of Participant Interactions With Packs:** We will employ the extensive 3D multimodal data collection capabilities offered by the Microsoft Kinect sensor (<http://www.kinect4windows.org>) and the Leap motion device (<http://www.leapmotion.com>) to augment video analysis during a first exposure to each pack design as well as detail changes in routinized behavior in response to intervention, and persistence of effects over time. The combination of the sensor tracking capabilities will allow us to quantify behaviors (body, finger and hand positions), visual attention (head direction), facial expressions (valence), verbal communication (directional audio) and pack movements (e.g. % of time oriented to side with warning label; % of time obscured). These indicators can be paired with participant reports to assess impact positive (approach) and negative (avoidance) reinforcing qualities of each pack and warning label design. Metrics obtained will be used to predict real-time changes in perceptions, report of tobacco-related harms, compliance with study pack use, and tobacco use behaviors during the three-month study evaluation period.

[figure not shown]

**9.B.5. The Conjoint Trade-off Project:** Participants will then complete a web-based conjoint analysis designed by consultant, [name] who is experienced in the conduct of these studies. Participants will complete a series of web-based choices between digitally altered images of packs at different price points, in a fractional factorial design. Each choice will ask the participant to rank a small subset of the possible packs and to provide individual ratings of pack images for personal relevance, believability, and aversiveness. The study will estimate the relative importance placed on each attribute, which will be of independent interest to the scientific community.

**9.B.6. Study Run-in Period:** We will use a 1-month run-in period prior to study enrollment. During this period, participants will be required to complete the TQ and text messaging assessment. Further, they will need to make at least 2 purchases of their usual brand of US packaged cigarettes from our study vendor (at a 10% discount over their usual price-assessed earlier). We will use text messaging on a pre-agreed schedule to prompt each purchase with a link to secure study hosted web-order forms. Successful completion of this run-in phase will be required in order for a participant to be considered for randomization. We will use the number of packs purchased/week as a flag for the maximum packs that can be purchased during the intervention to eliminate the possibility of participants reselling cigarettes for profit. Any higher amount requested will trigger a study investigatory contact and approval.

**9.B.7. Cigarette Products:** We will purchase standard brand cigarettes from local vendors and coordinate repackaging with our Consultant team. We will fill PP and AM packages with US branded cigarettes. We have worked previously with the company that does the re-packaging and has evidence that smokers do not differentiate the final product from the usual industry product.

**9.B.8. Randomization to the study arms:** We will use a permuted blocks randomization scheme to allocate participants to one of 3 study arms. We will stratify on 2 categories of total consumption history ( +/- >5 pack years smoked total) crossed with 2 categories of quitting history (+/- 7+ days abstinence in past year).

**9.B.9. Assessment through SMS Text Messaging:** We have partnered with HealthCrowd, a vendor experienced in clinical research to provide 2-way SMS messaging with participants. This validated method will allow us to track and report the performance of participants, and allow participants to alert study staff to needs for product delivery, without reliance upon scheduled phone contacts. We will use SMS to flexibly administer both weekly or daily behavioral assessments.

**9.B.10. Using Pricing as a Motivational Tool:** The study will offer all cigarettes at a discount from the usual price at local discount stores, as an incentive to use study cigarettes. For participants that have not fulfilled their expected purchase amount within a week of their scheduled purchase, the study will contact them and

investigate whether they have quit or significantly reduced their smoking. Should the reason be that they purchased from another supplier, we will use a further price incentive (additional 10% discount) to encourage them to stay in the study intervention; participants will not be aware of this option in advance. If required, we are prepared to discount the cigarettes as much as 50% to maintain participants on the study protocol.

However, we will not provide these participants with MORE packs per week than they smoked during the one month run-in period to reduce the potential risk of entrepreneurs re-selling cigarettes for profit.

**9.B.11. Study Questionnaire:** We will assess tobacco use behavior, cognitions, and affect using nationally validated measures drawn from the FDA/NIDA sponsored PATH survey (Drs [name], [name] and [name] are members of the Scientific Investigators group). This will assure compatibility with other large federally sponsored surveys as PATH measures have been harmonized with the Tobacco Use Supplement to the Current Population Survey and the National Health Interview Survey as well as questions from the Australian surveys conducted by consultant [name]. We will use the modular web-based survey (TQ).

**9.B.12 Saliva Sample:** *Salivary cotinine* will be used to measure exposure to nicotine, which may stem from changes in either cigarette or NTP consumption. Saliva will be collected via passive drool into 2mL cryovials, and a minimum 75 ul saliva collection volume immediately verified. Salivary cotinine will be biochemically analyzed in duplicate using Enzyme-Linked Immuno Sorbent Assay (ELISA) kit from Salimetrics, USA.

**9.B.13 General statistical analysis plan.** The study team has extensive experience presenting analyses from longitudinal data and includes strong biostatistical expertise (**[name] and [name]**). We are confident that we will use rigorous and up-to-date inferential methods, while retaining interpretability of the analysis and results. For each aim and hypothesis, we will pre-specify the outcome measure and time point, and the predictors of interest. Models will include the stratification variables for the randomization (consumption level and quitting history). Models will control for a standard set of potential confounders, including age, gender, race/ethnicity, peer and family influences, addiction level, and presence of anxiety disorders. Primary analyses will use logistic regression, a linear, or generalized linear model depending on whether the outcome of interest is binary, continuous or ordinal-scaled. When using data across time points, if needed, we will use a random effects model or generalized estimating equations to control for within subject correlation, in a repeated measures framework. **Power and sample size** With 450 subjects we will have 150 in each arm, Standard US pack (ST), Plain pack (PP), and Plain pack+Graphic warning (Australian Model: AM). We assume 20% dropout, occurring uniformly over the study period. For each outcome measure, the primary effects of interest are the contrasts ST-(PP and AM) and PP-AM, with the expectation that the AM effect will be larger than the PP. We conducted power analysis for the contrast with the smallest sample sizes (PP-AM), using a Fisher exact test or a 2 sample t-test for comparison of effects at the end of study; and, for comparison of in within-subject trends over time, by simulation using a generalized linear mixed effects models (GLMM). We aimed to estimate the effect size we can detect with 80% power, using a 2-sided test of hypothesis at significance level 0.025 to correct for the 2 primary contrasts of interest. For a longitudinal change measured over the three-month intervention period, results from 1000 simulations suggest power >0.85 for expected medium effect sizes in mean differences.

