## 20. COMPENSATION FOR PARTICIPATION

Participants will be compensated \$20 if they successfully complete the initial baseline visit and provide a saliva sample during the run-in period. During run-in they will purchase their usual brand of cigarettes at a 10% discount from the study vendor. Following randomization, they will continue to purchase discounted cigarettes but with packaging according to study design for the intervention period; however, should they miss a scheduled purchasing point and indicate that they have purchased their usual brand elsewhere, they will be offered an additional discount to incentivize them to get back on the study protocol. After completion of the intervention period, smokers will no longer have access to discounted cigarettes from the study vendor. At 5 and 12 months, participants will receive \$40 for completion an additional web-based survey and provision of a saliva sample at each of these assessments. Finally, if they have completed all assessments in the study, they will receive an additional \$60 at the end of the study. Thus, the total incentive for all participants in the study, regardless of study arm, will be \$160.

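### The protocol places the second visit both at the end of purchasing (month 4 from baseline) and at month 5, with no time origin or window to settle which

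*Protocol*

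**What the plan says.** **Length of the periods.** Section 9.B.1.a: "There will then be a 1-month run-in period during which they will purchase their US branded cigarettes from the study". Section 9.B.1.b: after randomization, "the purchasing intervention will last 3 months". Section 9.B.3 adds these up from the baseline visit, where participants commit to the study website "as their only vendor for cigarettes for the next 4 months (1-month run-in and 3-month intervention". Section 9.B.1.c then ends use of the study packs: "After 3 months, participants will go back to purchasing cigarettes from their usual sources and follow-up will continue through 12 months". Section 20 agrees that access to the discounted study cigarettes ends with the intervention.

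**Second visit, dated by event.** Section 9.B.1.d sets clinic visits at the start of the run-in and "at the end of both the purchasing and the post intervention periods". Each visit carries a web questionnaire, a saliva sample and the recorded handling tasks.

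**Second visit, dated by calendar.** Later in the same section: "Using the self-report assessments at baseline, 5- and 12-month visits". Section 20 pays for a survey and "provision of a saliva sample at each of these assessments", meaning those at 5 and 12 months.

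**What the visit has to support.** Aim 3b expects "greater reductions in tobacco use during the 3-month intervention, validated by saliva cotinine". Section 9.B.1.d also wants pack handling assessed once participants have used their assigned packs for three months, which serves Aim 3a.

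**The concern.** The two datings of the second visit do not agree, and the difference decides whether it takes place on or off the assigned packs. It is the only visit after randomization that can yield saliva, laboratory handling data and a web questionnaire close to the intervention. The next one is at month 12.

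The month-5 label appears in two separate sections, one of which governs payment, so staff could reasonably schedule from it. PP and AM participants would then be back on branded packs. All arms would also have lost the study price, which starts at a 10% discount and may reach 50% for some participants. Consumption, cotinine and handling would be measured under conditions other than those being tested. Aim 1b itself expects the arms to differ less after the intervention than during it.

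**Working it through.** **Inputs (all from the protocol).** Run-in 1 month (9.B.1.a); purchasing intervention 3 months (9.B.1.b); calendar label of the second assessment, month 5 (9.B.1.d and section 20).

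**Step 1: reproduce the plan's own figure.** Run-in + intervention = 1 + 3 = 4 months. This matches the 4 months in section 9.B.3. Assigned packs stop at month 4 from baseline, or month 3 from randomization.

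**Step 2: compare with the label.**

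| Time origin | Assigned packs stop | Label | Gap |
|---|---|---|---|
| Baseline visit | month 4 | month 5 | 5 − 4 = 1 month |
| Randomization | month 3 | month 5 | 5 − 3 = 2 months |

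On neither clock is month 5 the end of purchasing. The text describes no interval between the end of purchasing and the second visit, and gives no visit window.

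**Step 3: which measurements depend on the answer.**
- *Saliva cotinine (Aim 3b).* Samples are tied to the three clinic visits. If the second is at month 5, none falls during or at the end of the three intervention months. Assuming cotinine reflects nicotine exposure over recent days, a sample taken one or two months later cannot validate use in that period.
- *Laboratory handling task (Aim 3a).* It would be recorded after PP and AM participants had resumed handling branded packs. ST participants have no packaging change to reverse.
- *Web questionnaire.* The same timing applies.
- *Text messages.* Section 9.B.1.d runs these through every study period, covering pack appeal, willingness to display, awareness of harms and quitting cognitions. These outcomes have on-pack data whatever the date of the second visit.

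**The case against.** The strongest reply is that the protocol already says the right thing. The opening of 9.B.1.d ties the second visit, with all its components, to the end of purchasing, so the month-5 label may be loose wording. A reader might infer that the trial is designed to measure its end-of-intervention outcomes about a month off the packs. The documents do not support stating that as fact: late measurement follows only if the label governs. This part of the reply stands.

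The time origin is also open. Section 11 has verbal consent and screening before the baseline visit, so a clock started there would shorten the gap. But no passage starts the clock there or gives that interval, and 9.B.6 places enrollment after the run-in, which points the other way. Figure 1 is not shown and may carry a schedule, but the text would still disagree with itself.

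Three further inferences go too far:

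- *That Aims 2a and 2b lose their intervention-period data.* They do not, because text messages collect these outcomes on-pack. For Aim 3b, purchase records and text messages also run during the intervention; the exposed part is the cotinine check.
- *That the power loss can be stated.* Take a 0.5 SD difference and decay of 0%, 25% or 50%, with power = Φ(d/√(2/n) − 2.2414) at two-sided 0.025. With n = 120 per arm (150 less the full 20% dropout), power is 0.95, 0.75 and 0.38. If dropout is uniform over 12 months, about 150 × (1 − 0.20 × 5/12) ≈ 137 per arm remain at month 5, giving about 0.97, 0.81 and 0.43. The 0.5 SD and the decay rates are assumptions, not protocol figures. Section 9.B.13 also bases its intervention-period power on simulated longitudinal change, not on a single t-test at month 5.
- *That the 12-month follow-up is misdescribed because only 12 − 4 = 8 months follow the packs on the baseline clock.* Section 9.B.1.c takes follow-up through month 12, and nothing promises twelve months after the packs stop.

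**Conclusion.** The contradiction is real and should be corrected before enrollment. Sections 9.B.1.a to 9.B.1.c and 9.B.3 end the assigned packs at month 4 from baseline, and the opening of 9.B.1.d puts the second visit there. The later text of 9.B.1.d and section 20 put it at month 5. The discrepancy is one month on the baseline clock and two on the randomization clock.

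The consequence is conditional. If the label is followed, the cotinine validation in Aim 3b fails for its stated period (given that cotinine reflects recent exposure), and the handling comparison in Aim 3a is made off the assigned packs. Any effect that fades once the packs stop would be diluted. Aim 1b is a hypothesis that such fading occurs, not evidence of its speed, so the size is unknown. If the event-based wording is followed, the gap is zero and none of this arises. On-pack saliva and handling data that are missed cannot be recovered later, which is why a wording conflict deserves correction.

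**What to change.** Reconcile sections 9.B.1.a to 9.B.1.d, 9.B.3 and 20:

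1. State the time origin for the 5- and 12-month labels.
2. Set the second questionnaire, saliva sample and handling visit in a short, stated window at the end of the purchasing period, before the assigned packs stop (month 4 from baseline, month 3 from randomization), as the opening of 9.B.1.d already intends.
3. Replace the 5-month label in 9.B.1.d and section 20 with that visit.

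The cost is protocol wording and visit scheduling. The number of visits and samples is unchanged, and so are the payments: $20 + $40 + $40 + $60 = $160, as section 20 states.

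### Section 9.B.13 does not name the pre-randomization value of the outcome as a covariate, which can cost precision for continuous outcomes compared at a single follow-up time

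*Protocol*

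**What the plan says.** Section 9.B.13 (General statistical analysis plan) chooses the model by outcome type: logistic, linear or generalized linear. It lists what goes in beside study arm. First, the stratifiers: "Models will include the stratification variables for the randomization (consumption level and quitting history"). Then: "Models will control for a standard set of potential confounders, including age, gender, race/ethnicity, peer and family influences", together with addiction level and anxiety disorders. The outcome's own baseline value appears in neither list.

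Three other statements in the section bear on the point:

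- Details are to follow: "For each aim and hypothesis, we will pre-specify the outcome measure and time point, and the predictors of interest".
- Data from several time points are handled conditionally: "if needed, we will use a random effects model or generalized estimating equations to control for within subject correlation, in a repeated measures framework". The text does not say whether baseline is a response, a covariate or absent from such a model.
- Power for the plain-pack versus Australian-model contrast was assessed "using a Fisher exact test or a 2 sample t-test for comparison of effects at the end of study", and by mixed-model simulation for trends within participants.

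Baseline data exist by design. Section 9.B.1.a says that at first contact "eligible participants will complete all baseline lab and self-report assessments", ahead of the one-month run-in and randomization. Section 9.B.1.d attaches a web questionnaire, a saliva sample and the recorded pack-handling task to each clinic visit, the first of which opens the run-in, and has text messages in every study period. Section 9.B.3 records the current smoking pattern at the first visit. Section 9.B.6 makes the questionnaire and the text-message assessment conditions for randomization.

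**The concern.** In a randomized trial the listed variables do not confound the comparison of arms in the usual sense; the reason to adjust for them is that they predict the outcome. By that criterion the first candidate for a continuous outcome is usually the same measure taken before randomization. Here it is available at no extra cost and should be close to complete, because the questionnaire and text-message assessments must be finished before a participant can be randomized.

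If the models are fitted with only the named covariates, a single-time-point comparison of a continuous outcome carries a larger standard error than the data require. This matters most for plain pack versus Australian model, which the protocol singles out as the contrast with the smallest sample sizes.

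**Working it through.** **Inputs from Section 9.B.13.** "With 450 subjects we will have 150 in each arm"; 20% dropout, so 150 × 0.8 = 120 per arm at the end of study; two-sided alpha 0.025; 80% power.

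**Input that is assumed.** The correlation rho between baseline and follow-up is not given. The range 0.3, 0.5, 0.7 is used.

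**The plan's own figures.** Alpha reproduces: 0.05 / 2 contrasts = 0.025. The simulated power above 0.85 for a medium effect cannot be rerun, because the numerical effect, SD, within-subject correlation and number of time points are not stated. As a plausibility check only, an end-of-study comparison at an assumed 0.5 SD with 120 per arm has power 0.949 (normal approximation) or 0.946 (t distribution). That is compatible with the stated figure but does not reproduce it.

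**Step 1: no baseline.** Detectable difference = (z for alpha + z for power) × sqrt(2/n) = (2.2414 + 0.8416) × sqrt(2/120) = 3.0830 × 0.1291 = 0.398 SD.

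**Step 2: baseline as a covariate.** The residual SD is multiplied by sqrt(1 − rho²). Power at difference d is Φ(d × sqrt(n/2) / sqrt(1 − rho²) − 2.2414).

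| rho | sqrt(1 − rho²) | detectable difference (SD) | variance removed | power at 0.4 SD | power at 0.5 SD |
|---|---|---|---|---|---|
| no baseline | 1 | 0.398 | none | 0.804 | 0.949 |
| 0.3 | 0.954 | 0.380 | 9% | 0.843 | 0.966 |
| 0.5 | 0.866 | 0.345 | 25% | 0.909 | 0.987 |
| 0.7 | 0.714 | 0.284 | 49% | 0.982 | 0.999 |

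**Step 3: does a repeated-measures or change analysis already do this?** It depends on how baseline enters. If baseline is a response with arm means left free, then with complete data the arm-by-time contrast at one follow-up is essentially a change-score comparison. Its SD factor is sqrt(2(1 − rho)), so the detectable difference is 0.471, 0.398 or 0.308 SD at rho 0.3, 0.5 or 0.7. Relative to that analysis, the covariate model has variance (1 − rho²) / (2(1 − rho)) = (1 + rho)/2 = 0.65, 0.75 or 0.85. If arm means are constrained equal at baseline, or baseline is a covariate, the loss largely disappears.

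**Sensitivity to n.** With no dropout (150 per arm) the baseline-free figure is 0.356 SD. The proportional gains in step 2 do not depend on n.

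**The case against.** The strongest reply is that the section leaves baseline unnamed without excluding it. The covariate list is open-ended, the predictors are still to be pre-specified for each hypothesis, and an SAP not available here may name baseline. This stands as a limit on how firmly the point can be put. It does not remove the point, because the section goes as far as naming individual covariates and describes the set by a rationale, confounding, that would not lead anyone to add the baseline outcome.

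Second, the t-test and Fisher test are sizing devices, and the planned models already hold consumption history, quitting history and addiction level. These may share variance with baseline smoking and cotinine, so the true gain is probably smaller than in the table. This stands.

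Third, Aims 2a and 3b are framed as change or reduction, and power was also simulated for longitudinal change. A repeated-measures model that includes baseline may already use much of the information. This stands in part: such models are to be used only where needed, and step 3 shows that the unconstrained form can still lose precision.

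Fourth, a reader might infer that the loss affects every measure and every primary outcome. The document does not support that. Nowhere does it say that every outcome has a usable baseline. Section 10 enrolls only daily smokers with no intention to quit within six months, so the quit-intention outcomes of Aim 3c have little baseline variation. For logistic models, adjustment changes the quantity estimated (a conditional odds ratio), and the SD formula does not carry over.

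Fifth, Section 9.B.1.d measures participant characteristics and environmental influences again at 5 and 12 months, so a reader might infer that post-randomization values would be entered and would bias the contrast. Section 9.B.13 gives no measurement time for its covariates and never says later values will be used. A one-clause safeguard is reasonable; a claim of bias is not.

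**Conclusion.** The point holds for continuous outcomes compared at a single follow-up time. The named covariate set leaves out the pre-randomization value of the outcome, although it is collected. The detectable difference could fall from about 0.398 SD to 0.380, 0.345 or 0.284 SD at rho 0.3, 0.5 or 0.7. This rests on 120 per arm, two-sided alpha 0.025, 80% power, assumed correlations, and no variance already explained by the other covariates. The gains are therefore best read as upper bounds.

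It is a matter of efficiency. The calculation does not show an underpowered trial: at an assumed 0.5 SD, power without baseline is already 0.949. The gain matters more if the plain-pack versus Australian-model difference is nearer 0.4 SD, where power without baseline is 0.804. The point does not extend to binary outcomes or to quit-intention outcomes restricted by eligibility, and it does not show that the plan would bias any contrast.

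**What to change.** Add to Section 9.B.13:

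1. Each primary model for a continuous outcome includes study arm, the two stratification factors and the pre-randomization value of the same outcome. For text-message items this is the run-in mean.
2. Repeated-measures models enter baseline either as a covariate or as a response with arm means constrained equal at baseline.
3. All other covariates are baseline values. They are better described as prognostic covariates than as confounders.

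The cost is two or three sentences. No new data, visits or participants are needed. The wording should be settled before outcome data are seen by arm. If an SAP already says this, a cross-reference is enough.
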